**Control**

**N=4**

**ASSESS-meso cohort**

# BACKGROUND

## Mesothelioma

Malignant pleural mesothelioma (MPM) is an aggressive tumour of the pleura with an increasing incidence globally and in the UK.^1-3^ The UK mortality rate for MPM is the highest in the world, with one person dying from the disease every 4 hours.^1-3^

The average survival with MPM is between 9 and 14 months from diagnosis.^1-7^ Treatment options are limited, with only one chemotherapy regimen available, offering a median survival benefit of 12 weeks.^4^ Recently, the addition of Bevacizumab to this regimen extended median survival to 18 months.^43^ Unfortunately, only 30% of patients with MPM receive chemotherapy, as co-morbidities and patient choice preclude its use in others.^2^

One of the reasons that MPM is so aggressive is that it evades immunological defences that usually inhibit tumour growth. Cytotoxic T Lymphocytes and Natural Killer cells, which usually respond to tumour antigens and limit tumour progression, are depleted in the pleura of patients with MPM.^8-11^ The ability to maintain intra-pleural T cell activity is associated with longer survival.^12-15^ Drugs that stimulate T cells have shown promise in MPM, with phase 3 trials underway.^16 17 44^

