## Inclusion criteria

To participate in TILT patients must meet all of the following inclusion criteria:

- Histological or cytological diagnosis of MPM
- Enrolled in ASSESS-meso and has given consent to be considered for and be randomly selected for future trials
- Functioning IPC in situ or IPC that has ceased to drain, but can be successfully flushed with 20mls of normal saline.

OR willing to have an IPC and has a pleural effusion suitable for IPC insertion

- No chemotherapy in preceding 4 weeks and none planned in subsequent 4 weeks
- Performance status ≤2, or PS 3 and felt clinically suitable for trial
- Predicted survival ≥12 weeks from enrolment
- Able to give written informed consent & meet trial requirements

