### 8.2.5 IPC removal

Once inserted, drains may be removed at any time at the discretion of the patient’s primary physician, at the request of the patient, or at the discretion of the trial team. Potential reasons for removal include subcutaneous or pleural infection, intolerable pain, significant fluid loculation, or successful pleurodesis. Reason for removal will be documented on eCRFs.

If a drain is to be removed, patients should be given an appointment to have this done within 14 days of the clinical assessment at which this decision was taken. Removal of indwelling pleural catheters should be performed by trained staff under aseptic conditions, and should be followed by a chest x-ray.

Any participant who has their drain removed during their trial period will continue to undergo planned follow-up for the full trial period. Drain removal will be documented on eCRFs.

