## Secondary outcome measures

Secondary outcome measures will collect exploratory data on the clinical efficacy of OK432 and BCG. This data will be used to decide the primary outcome for the subsequent full-scale trial, and to estimate the variance of the chosen outcome for a sample-size calculation. Potential outcomes include:

- Tumour response, based on CT appearances at baseline and 12 weeks ^42^
- Overall survival (OS), defined as time between date of diagnosis with MPM to date of death, censored 12 weeks after the final trial visit of the final participant
- Progression-free survival rates (PFSR) at 12 weeks
- Patient-reported chest pain and breathlessness, measured on visual analogue scales (VAS)
- Patient-reported quality of life, measured using the EQ-5D-5L health questionnaire
- Pleurodesis rates, defined as pleural fluid drainage of less than 50ml on 3 consecutive occasions, with <25% opacification on CXR or <250ml pleural fluid on thoracic ultrasound scanning (TUS)
- Time to pleurodesis, calculated from baseline assessment to date of pleurodesis
- Biomarker response assessed using serial serum and pleural mesothelin levels

Participants will be followed up until death, or end of trial (EoT) 12 weeks after the final trial visit of the final participant, whichever is sooner.

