## Analysis plan

Basic descriptors will be used to summarise the characteristics of the overall trial population, each arm, and participants who decline any element of the trial. The characteristics of people who decline participation will be compared with the trial population using means, confidence intervals, chi-squared and unpaired T-tests. If possible, multivariable regression modelling will be undertaken to explore which factors were associated with non-acceptance of OK432/BCG.

Feasibility outcomes, including recruitment, randomisation and trial completion rates, will be described for the overall trial and for each arm. Secondary outcomes will be summarised for each arm based on randomisation, i.e. intention to treat. Per protocol and compliance averaged causal effects (CACE) analysis will be undertaken as secondary analyses for clinical efficacy outcomes.

Time to event data will be analysed using the Kaplan-Meier method. Cox proportional hazards modelling will be used to calculate hazard ratios for death and pleurodesis. Univariable modelling will be used, followed by multi-variable methods to control for potential confounders. The time-independent confounders to be considered are age, sex, performance status, tumour histology and whether chemotherapy was received. Time-dependent confounders that will be adjusted for are the time between diagnosis with MPM and baseline assessment, and length of time the IPC was in situ. The main analysis will include all patients. A priori sub-group analyses will stratify patients according to time since diagnosis (≥8 weeks versus <8 weeks) and whether chemotherapy was received.

Pleurodesis rates will be calculated for the whole population, and in the sub-group of patients who’s IPC had been in situ for less than 6 weeks at baseline assessment.

Outcomes with repeat measurements, e.g. PROMS and biomarker responses, will be analysed using regression modelling with adjustment for baseline values. Survival rates will be compared with national survival data, and survival rates from previous clinical trials of new treatments in MPM. Progression-free survival rates will be compared to validated values for acceptable clinical activity of new oncological agents in MPM.^99^

Statistical analysis will be undertaken using Stata (StataCorp LP) version 14, with support from YTU.

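### Time to pleurodesis is analysed by Kaplan-Meier with death acting as censoring, which overstates the probability of pleurodesis; the effect is minor at this sample size

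*Protocol*

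**What the plan says.** Section 13.2 of the protocol (Secondary outcome measures) lists "Time to pleurodesis, calculated from baseline assessment to date of pleurodesis". Death is not part of that event. The same section sets the end of follow-up at the earlier of two points: "Participants will be followed up until death, or end of trial (EoT) 12 weeks after the final trial visit of the final participant, whichever is" […].

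Section 13.3 (Analysis plan) fixes the methods. "Time to event data will be analysed using the Kaplan-Meier method", without exception, and then "Cox proportional hazards modelling will be used to calculate hazard ratios for death and pleurodesis". No competing-risk method is named. A pleurodesis rate is to be calculated separately, in the whole population and in a subgroup defined by how long the catheter had been in place.

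Two other places bear on the point. Section 8.2.4 defines pleurodesis by three consecutive low-volume drainages plus imaging. Section 8.2.5 says "Potential reasons for removal include subcutaneous or pleural infection, intolerable pain, significant fluid loculation, or successful pleurodesis", and keeps participants whose drain is removed under planned follow-up for the rest of the trial period.

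**The concern.** Kaplan-Meier treats a censored participant as still able to have the event later, at the same rate as those who remain under observation. That is reasonable for someone who reaches the end of the study. It is not reasonable for someone who has died, because death rules pleurodesis out. With follow-up ending at death and no other rule given, a death without pleurodesis can enter the estimate only as censoring. One minus Kaplan-Meier then describes a setting in which nobody dies, not the share of patients who achieve pleurodesis.

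Deaths are foreseeable. The Background gives "The average survival with MPM is between 9 and 14 months from diagnosis". Eligibility asks for "Predicted survival ≥12 weeks from enrolment", but section 10.5 concedes that such predictions are unreliable, and section 12.2 lists death from the malignancy as expected. Section 13.2 intends the secondary outcomes to help choose the main endpoint of the later full-scale trial and to inform its sample size. Pleurodesis is one of the candidates, so an optimistic probability could be carried forward.

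**Working it through.** The protocol gives no expected pleurodesis probability or death count, so there is no figure to reproduce. The check has four parts.

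**1. Small arms, exact.** The trial flowchart shows 4 per arm, and section 13.3 summarises secondary outcomes by arm. Take the order of events in one arm, with the remaining participants event-free to the end.

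- Death, then one pleurodesis. After the death 3 remain at risk, so 1 − KM = 1 − (1 − 1/3) = 33%. Cumulative incidence (Aalen-Johansen) = (3/4) × (1/3) = 25%, which is the plain proportion, 1 of 4.
- Death, then two pleurodeses. 1 − KM = 1 − (2/3)(1/2) = 67%. Cumulative incidence = 1/4 + 1/4 = 50%, or 2 of 4.
- Two pleurodeses, then a death. 1 − KM = 1 − (3/4)(2/3) = 50%, and cumulative incidence is also 50%.

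The error therefore arises only when a death precedes a pleurodesis.

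**2. How likely deaths are.** Assumption: the documents' 9 to 14 months is an exponential median counted from baseline. The death hazard is hd = ln 2 / median, with medians of 39.1 and 60.9 weeks. By 12 weeks, 1 − exp(−12·hd) = 19.1% (9 months) or 12.8% (14 months). Among 12 participants that is 2.3 or 1.5 expected deaths. The chance of at least one is 1 − (1 − 0.191)^12 = 92%, or 1 − (1 − 0.128)^12 = 81%.

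**3. Expected overstatement.** Assumption: constant hazards, with the pleurodesis hazard hp = −ln(1 − p)/12 for an assumed net probability p of 20%, 40% or 60% at 12 weeks.

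- Deaths censored: 1 − KM = 1 − exp(−hp·t)
- Death competing: CIF = hp/(hp + hd) × [1 − exp(−(hp + hd)·t)]

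| Week | p at 12 weeks | 1 − KM | CIF, 9-month median | CIF, 14-month median | Overstatement, points (9 / 14 months) |
|---|---|---|---|---|---|
| 12 | 20% | 20.0% | 18.1% | 18.7% | 1.9 / 1.3 |
| 12 | 40% | 40.0% | 36.4% | 37.6% | 3.6 / 2.4 |
| 12 | 60% | 60.0% | 54.9% | 56.7% | 5.1 / 3.3 |
| 24 | 20% | 36.0% | 29.8% | 31.8% | 6.2 / 4.2 |
| 24 | 40% | 64.0% | 54.0% | 57.3% | 10.0 / 6.7 |
| 24 | 60% | 84.0% | 72.7% | 76.4% | 11.3 / 7.6 |

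Week 24 is relevant because the end of trial in section 13.2 falls 12 weeks after the last participant's final visit, which is itself at week 12. Even the last recruit, if alive, would be followed for about 24 weeks.

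**4. Against sampling error.** For a proportion of 40% in an arm of 4, the standard error is √(0.4 × 0.6 / 4) = 0.245, about 24 points. The 12-week overstatement of 1.3-5.1 points is a small fraction of that. The largest 24-week figure, 11.3 points, is about half of the matching standard error, √(0.727 × 0.273 / 4) = 0.223.

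**The case against.** The strongest reply is that little depends on this. TILT is a 12-person feasibility study, pleurodesis is one of several exploratory outcomes, and no decision rule uses the curve. The pleurodesis rate is reported separately, and the protocol nowhere says that 1 − KM will serve as that rate or pass into the next trial's design. All of this stands and sets the severity. It does not make Kaplan-Meier the right estimator, and the protocol has chosen that method explicitly, so this is not a detail left open for a later analysis plan.

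Three stronger readings may tempt a reader, and the protocol does not support them.

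- **That catheter removals for infection, pain or loculation are also censored.** Nothing says so. Section 8.2.5 keeps these participants in follow-up. Kept at risk as non-events, they do not inflate the estimate. It is true only that the three-drainage definition cannot be newly met once the drain is out.
- **That the comparison between arms is invalid if mortality differs.** The stated comparison is a Cox hazard ratio, which remains valid as a cause-specific hazard ratio. In the model above, 1 − KM does not contain the death hazard at all. What is wrong is reading the curve as an achieved proportion.
- **That the overstatement is 12 to 21 points.** The same formulas do give 12.0-21.5 points at 52 weeks, but only if pleurodesis goes on occurring at a constant rate for a year after a single dose. The schedule of visits ends at week 12, and section 9.6 defines an earlier end of trial than section 13.2. If few pleurodeses occur after week 12, the gap stays near its 12-week size.

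**Conclusion.** The point holds for deaths and is minor. As written, section 13.3 censors participants who die without pleurodesis, and 1 − KM overstates the probability of pleurodesis whenever a death comes first. The arm-of-4 examples need no assumption beyond the order of events.

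The expected sizes, about 1-5 points at 12 weeks and 4-11 at 24 weeks, are illustrations. They rest on constant hazards, on an assumed 20-60% net pleurodesis at 12 weeks, and on a survival figure that the protocol gives from diagnosis but that is used here from baseline. The true death rate after enrolment could be higher or lower. The overstatement grows later only if pleurodesis continues to occur. At this sample size it is small against sampling error, and the primary feasibility conclusion is unaffected.

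**What to change.** In section 13.3:

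- Restrict Kaplan-Meier to overall survival and progression-free survival.
- Report time to pleurodesis as cumulative incidence (Aalen-Johansen), with death without pleurodesis as a competing event.
- Keep the Cox model for pleurodesis and label its result a cause-specific hazard ratio.
- State that participants whose catheter is removed for another reason are not censored at removal, and are counted as not pleurodesed.

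The cost is a short edit and a standard routine in the planned software, with no new data and no change to trial conduct. The downside is that the reported pleurodesis probability becomes slightly less favourable.

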# ETHICAL CONSIDERATIONS

## Indwelling pleural catheters

The use of IPCs to manage malignant pleural effusions is standard practice in many centres in the UK and worldwide. Consequently there are no predicted ethical issues regarding their use in this study, especially since the majority of participants are expected to already have an IPC in situ. Participants without an existing IPC must be willing and able to have one inserted in order to be eligible for TILT.

## OK432

OK432, as used in the context proposed in this trial, is regarded as an IMP and the appropriate approval will be sought from the MHRA and HRA. .

Intra-pleural OK432 is an established treatment for malignant pleural effusions in Japan, South Korea and Taiwan. Since its launch in 1975 adverse event reporting has revealed no significant adverse reactions greater than grade 2 severity. Safety data of intra-pleural OK432 in people with MPM will be collected throughout TILT. Participants who are offered OK432 will be made aware of OK432’s unlicensed status in the UK, and will be asked to provide consent to receive an IMP.

## BCG

Intra-pleural BCG, as used in the context proposed in this trial, is regarded as an IMP and the appropriate approval will be sought from the MHRA and HRA

Intra-pleural BCG has previously been used in patients with lung cancer following thoracic surgery. As well as mild, self-limiting systemic inflammatory symptoms, such as fevers, malaise and fatigue, the most common complication following BCG administration was would infection, bacterial or BCG pleural infection and chronic chest pain. Many of these adverse events are likely to relate to the delivery of a live agent into an area that had recently undergone a major surgical intervention. For this reason, recent thoracic surgery or intervention is an exclusion criteria for TILT.

Disseminated BCG is a rare but important risk associated with both intra-pleural and intra-vesical BCG delivery. Participants will be monitored for signs of disseminated BCG at every trial visit. TSP06b will include guidance on the diagnosis and management of disseminated BCG infection in TILT participants. Participants who are offered BCG will be made aware of all the associated risks, and will be asked to provide consent to receive it.

## Qualitative interviews

There is a possibility that the qualitative interviews may raise sensitive or upsetting issues in this population of patients with an incurable disease. However, consultation with patients has identified enthusiasm to discuss their experiences with clinicians. Interview content will be reviewed by a specific mesothelioma patient and public engagement group to ensure it is acceptable. Additionally, all participants will be given the contact details of a mesothelioma specialist nurse in case they require further support following the qualitative interviews. Anyone who finds the interviews particularly distressing will be offered referral to an NHS clinical psychologist.

## Focus group sessions

Existing qualitative research has demonstrated that the responses of partners, carers and relatives of people with MPM can differ significantly from that of the patient. Previous qualitative work with relatives revealed intense passion and anger, and the feeling that their role was to “fight for their loved ones, [who] were too ill to fight for themselves”.^85^ It is anticipated, therefore, that the focus group sessions may be more animated and impassioned than the individual participant interviews. All participants in the focus groups will be given the contact details of a mesothelioma specialist nurse in case they require further support, and anyone who finds the interviews particularly distressing will be offered referral to an NHS clinical psychologist.

It is recognised that the experiences of relatives/carers will be different depending on which arm of TILT their relative participated in. Therefore, if the focus groups were made up of a mixed group of relatives/carers, there is a risk of potential conflict or distress. For example, the relative of a participant in the observational arm may resent the partner of a participant who was offered OK432 or BCG. Conversely, people whose partners were not offered bacterial immunotherapy may feel angry towards the partner of a participant who was offered OK432 or BCG but declined it. Finally, the wife of a patient who declined immunotherapy may find it upsetting to hear the experiences of people who received it, particularly if the overall experience was positive, and may end up become angry at their partner for declining treatment.

For these reasons, separate focus group sessions will be held based on which arm of the study the associated participant of the relative/carer participated in. Where the number of relatives/carers associated with a particular trial experience is small, e.g. the relatives/carers of participants who were offered OK432 or BCG but declined it, individual qualitative interviews will be offered.

## Qualitative interviews with bereaved relatives

Ethical approval will be sought to contact the primary relative/carer of participants who have died during the course of TILT. The research team will send a letter to the bereaved person, thanking them for their relative’s participation in the research and inviting them to take part in a one to one qualitative interview with [name].

It is recognised that for the bereaved person, this will be an emotionally difficult time, and they may not wish to have any further interactions with the research (or clinical) team. Relatives who do not respond to the letter will not be contacted again.

If bereaved relatives do wish to participate in qualitative interviews, they will be given the choice of where and when the interview is held. This is because they may prefer not to return to the hospital where their relative was treated. Additionally, if they wish to have a friend or family member present during the interview, this will be allowed. It is not anticipated that the interviews will be distressing in themselves, however it is appreciated that this will be a difficult and emotional time for relatives. Therefore, if a relative becomes distressed at any point the interviewer will ask them whether they would like to stop, and will terminate the interview if they say yes. If the relative wishes to continue, then the interviewer will do so but will check again later that they are OK to continue. All relatives who express significant distress during an interview will be offered referral to an NHS clinical psychologist and all participants in the study will be provided with a list of useful further contacts for support.

## Consent and withdrawal

Participants must have full capacity to provide consent for the trial, as defined by the Mental Health Capacity Act 2005. To be eligible for TILT, participants must have already provided written, informed consent to join ASSESS-meso. The ASSESS-meso consent form will specifically refer to the use of participants’ data to identify additional trials they may be eligible for, and that they may be randomly selected to be invited to join such trials in future. Participants who have not consented to this element will not be eligible for TILT.

In this way, random selection can be undertaken on all eligible participants without requiring further TILT-specific consent. Participants who are not randomly selected to receive bacterial immunotherapycontinue observational follow up in ASSESS-meso, without undergoing any TILT-related interventions. Consequently they are not required to provide further consent.

Participants who are randomly selected to receive OK432 or BCG will be given detailed information about TILT and about the investigational medicinal product. They will have the opportunity to discuss the trial further with a member of the trial team. Participants will generally have 24 hours ‘thinking time’ to consider enrolling in the trial, although it is recognised that clinical circumstances may sometimes make this impossible. Participants will be asked to provide written, informed consent to participate in TILT, and for the collection of information about their care and collection of subsequent data sheets. Participants will be assured that their data will be stored securely and anonymously (see sections 14.5 and 14.6).

The right of the participant to refuse to participate in the trial without giving a reason is respected. However, specific ethical approval will be obtained to ask patients who decline trial participation to briefly give their reasons. In addition, these participants will be invited to participate in qualitative interviews exploring the acceptability of the research to them and their family members/carers.

Similarly, participants remain free to withdraw at any time from trial follow-up without giving reasons and without prejudicing their further treatment. These participants will remain within the trial for the purpose of follow-up unless the participant has specifically withdrawn consent for such follow-up. See section 11 for further information about withdrawal of consent.

